## Abstract

**Background:**

Pelvic organ prolapse (POP) is a common health problem. The lifetime risk of undergoing surgery for prolapse is 11%. POP significantly affects the effects on quality of life and activities of daily living. Laparoscopic sacrocolpopexy (LSC) has been viewed as the gold standard treatment for women with POP who desire reconstructive surgery. However, LSC is associated with technical difficulties, resulting in a long learning curve and operative time. Recently, our team introduced a new laparoscopic technique of inguinal ligament suspension (LILS) and had confirmed its safety and efficacy in treating vaginal vault prolapse. As a new surgical technique for POP, a prospective randomized controlled trial comparing the LILS with the standard technique of LSC is necessary. Therefore, we will conduct a trial.

**Methods:**

The trial is a randomized controlled trial. It compares LILS with LSC in women with stage 2 or higher uterine prolapse. The primary outcomes of this study are perioperative parameters, including surgical time, blood loss, intraoperative complications, and hospital stay as well as surgical anatomical results using the pelvic organ prolapse questionnaire (POP-Q) classification at 6 weeks, 6 months, 12 months, and annually till 5 years after surgery. Secondary outcomes are subjective improvement in urogenital symptoms and quality of life, postoperative complications, postoperative recovery, sexual functioning, and cost-effectiveness at each follow-up point. Validated questionnaires will be used and the data will be analyzed according to the intention-to-treat principle. Based on an objective success rate of 90%, a noninferiority margin of 15%, and a dropout of 20%, 107 patients are needed in each arm to prove the hypothesis with a 95% confidence interval.

**Discussion:**

The trial is a randomized controlled, multicenter, noninferiority trial that will provide evidence whether the efficacy and safety of LILS is noninferior to LSC in women with symptomatic stage 2 or higher uterine prolapse.

**Trial registration:**

China Trial Register (CTR): ChiCTR-INR-15007408. Registered on 9 November 2015.

**Electronic supplementary material:**

The online version of this article (10.1186/s13063-018-2494-x) contains supplementary material, which is available to authorized users.

## Background

Pelvic organ prolapse (POP) is a common condition that negatively affects substantial discomfort, quality of life and activities of daily living of up to 40% of all women [1]. With the aging, informed, and active female population, there is a growing need for high-quality and cost-effective treatment options for POP [2]. While various procedures have been designed to treat POP, until now the most successful method has been laparoscopic sacrocolpopexy (LSC), with overall objective anatomical and subjective success rates of 92% and 94.4%, respectively [3]. In this procedure, a mesh graft is used to attach the anterior and posterior walls of the vagina to the anterior longitudinal ligament at the sacral promontory. It provides an excellent cure rate, durability and low morbidity, and has been considered to be the gold standard procedure for POP [3–5].

However, LSC is technically more challenging because it requires surgical skills to perform suturing with knot tying. In addition, dissection to safely access the anterior longitudinal ligament at the level of the promontory may be a challenge, particularly for obese women, dense abdominopelvic cavity adhesions, large common iliac arteries, or when an anatomical variation exists. The procedure usually involves, in various deficiencies such as intrusion to the area of the retroperitoneal nerve plexuses, nonphysiologic placement of the vagina, and attachment to the sacrum associated with certain risks of vascular complications [6]. Thus, the technique is usually reserved for experienced surgeons who have excellent orientation in the anatomical structures of the lesser pelvis with particular focus on the rectovaginal and retroperitoneal pelvic floor space. These factors limit the popularization of this technique.

The inguinal ligament is a very important structure for surgery; it acts as a strong anchor or origin for the abdominal wall musculoaponeurosis [7]. In hernia surgery, the inguinal ligament is usually introduced as an attachment point of the conjoined tendon and transversus abdominis muscle-tendon to enhance the front and back wall of the inguinal canal [8]. Thus, the inguinal ligament has a relative fixed position and powerful tension. In addition, the portion of the inguinal ligament between the entrance of the inguinal canal and anterior superior iliac spine, especially for 1–2 cm distance from anterior superior iliac spine, presents two major characteristics: (1) a broad width with strong tension; (2) no large vessels and nerves around it. Thus, we hypothesized that the portion of the inguinal ligament, especially for 1–2 cm distance from anterior superior iliac spine, can be used as an anchor point for suspending the vaginal cuff.

Our previous study had confirmed that laparoscopic inguinal ligament suspension (LILS) could achieve excellent outcomes with higher anatomical and subjective cure rates and lower intra- and postoperative complications for vaginal vault prolapse [9]. As a new surgical technique for POP, a prospective randomized controlled trial comparing the LILS with standard technique of LSC is necessary. The aim of this study is to describe the rationale and design of a prospective randomized trial for comparing the efficacy, safety, and feasibility of LILS with LSC in the treatment of POP.

## Methods/Design

### Study objective

The aim of this randomized controlled trial is to compare LILS and LSC in the treatment of stage 2 or higher POP in terms of perioperative parameters, such as surgical time, blood loss, intraoperative complications, and hospital stay as well as objective and subjective success rates, recurrence of prolapse, functional recovery, quality of life, postoperative complications, sexual functioning, and cost-effectiveness.

### Hypothesis

Our hypothesis for this study is that there is no difference in anatomical success rate and patients’ satisfaction of the anterior, posterior, and apical compartment between laparoscopic inguinal ligament suspension and laparoscopic sacrocolpopexy in symptomatic women with uterine descent pelvic organ prolapse questionnaire (POP-Q) stage 2 or higher. Possibly, LILS may be associated with shorter surgical time, less blood loss, fewer intra- and postoperative complications, and more improvement of sexual functioning than LSC.

**Fig 1 Fig1:**
[figure not shown]
Study flow diagram

**Fig 2 Fig2:**
[figure not shown]
SPIRIT figure

### Study population and recruitment

All women seeking treatment for symptomatic POP with uterine descent POP-Q stage 2 or higher will be considered for inclusion in the trial. Patients with co-existing anterior/posterior defects or concomitant incontinence surgery can also be included.

Women with a surgical history for POP, known malignancy or abnormal cervical smears, a desire to preserve fertility, abnormal ultrasound findings of the uterus or ovaries or abnormal uterine bleeding, and contraindication for laparoscopic surgery are excluded from the study. Individuals who are unable to provide informed consent or to complete the testing or data collection are also excluded.

Eligibility is assessed by a gynecologist and/or residents of our hospital. Patients eligible for participation are counselled on the long duration of follow-up that is involved in the study. The risks associated with uterus removal are clearly outlined. Subsequently, women are provided with verbal and written information prior to enrollment, and written informed consent is obtained.

### Primary and secondary outcomes

The primary outcomes of this study included perioperative parameters such as surgical time, blood loss, intraoperative complications, hospital stay, and anatomical success rate using the POP-Q classification at 6 weeks, 6 months, 12 months, and annually till 5 years after surgery. The POP-Q system has been developed by the International Continence Society and is a reliable and reproducible method for assessing organ descent [10]. The lowest level of organ descent during Valsalva is measured relative to its distance from the hymen: points above the hymen are negative and those below are positive; vaginal support at the level of hymen is represented as ‘0 cm’. The anatomical success rate is defined as less than stage 1 (all vaginal sites at least 1 cm above the hymen on Valsalva), as scored by the POP-Q system. Secondary outcomes of this study include subjective outcome and improvement in general and disease-specific quality of life, short- and long-term complications, postoperative recovery, sexual functioning, and cost-effectiveness after LILS or LSC at each follow-up point.

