## Statistical analysis

### Sample size and power considerations

The sample size for this trial was estimated based on the hypothesis that both interventions are equivalent in anatomical success rate within a 1-year follow-up. A review [13] including 12 publications [14–24] showed an objective success rate of 78% to 100% for LSC. Thus, the sample size was calculated based on objective success rates of 90% within 1 year. If a two-sided alpha level of 5% was applied, then 89 individuals per group would be required to achieve a power of 1-β = 80% for a noninferiority margin of 15%. The rate of loss to follow-up without recurrence of prolapse is expected to sum up to 20%. Finally, a total of 214 participants (107 for each group) will be needed. Anatomical success rate at each follow-up point assessed by a POP-Q-examination in both study groups will be considered as primary outcome. Surgical anatomical success rate is defined as less than stage 1 (all vaginal sites at least 1 cm above the hymen on Valsalva), as scored by the POP-Q system. Noninferiority of LILS to LSC will be concluded if the lower limit of the 95% confidence interval in anatomical success rates lies above the noninferiority margin of -15% [25].

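### Primary anatomical success rests on POP-Q status at the visit alone, so a woman re-operated for recurrence can score as a success; if LILS fails more often, this can favour noninferiority

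*Protocol article*

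**What the plan says.** The protocol article defines the anatomical endpoint twice, in the same terms. Primary and secondary outcomes: "The anatomical success rate is defined as less than stage 1 (all vaginal sites at least 1 cm above the hymen on Valsalva". Sample size and power considerations: "Surgical anatomical success rate is defined as less than stage 1 (all vaginal sites at least 1 cm above the hymen on Valsalva". The latter section also fixes when it is scored: "Anatomical success rate at each follow-up point assessed by a POP-Q-examination in both study groups will be considered as primary outcome". Visits are at 6 weeks, 6 months, 12 months and then yearly to 5 years. Noninferiority is concluded if the lower 95% confidence limit for the difference in success lies above -15 percentage points.

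Data analysis specifies intention to treat, so a woman who has a second operation stays in her randomized arm.

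Recurrence appears elsewhere but is not tied to the endpoint. Study objective lists it as a separate comparison ("recurrence of prolapse, functional recovery, quality of life, postoperative complications"), Ethics has the DSMB look at recurrence rates, and the dropout assumption mentions it: "The rate of loss to follow-up without recurrence of prolapse is expected to sum up to 20" per cent. No section says how reoperation or other retreatment before a visit is scored.

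**The concern.** Success depends only on what the examiner finds on the day. Suppose a repair fails after the 6-month visit, the prolapse is operated on again, and support is good at 12 months. By the written definition that woman is a 12-month success of her randomized operation, although that operation failed.

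In a noninferiority trial, errors that pull the arms together are the ones to guard against. If the new operation really fails more often, it has more failures available for conversion into successes, and a true deficit looks smaller than it is. The yearly intervals after month 12 leave more time for failure and repair between two examinations.

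**Working it through.** **The plan's own figures.** Inputs from Sample size and power considerations: success 90% in both arms, margin 15 points, two-sided alpha 5%, power 80%, 89 per group, 107 after a 20% allowance for loss. The usual formula gives n = [0.90×0.10 + 0.90×0.10] × (1.960 + 0.842)² / 0.15² = 62.8, so 63 per group. The stated 89 is not reproduced. That is a separate matter and nothing below depends on it. The evaluable number used here is 107 × 0.80 = 85.6, taken as 86 per arm.

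**Scoring rule.** Let p be true success with a re-operated woman counted as a failure, and f the share of failures retreated and anatomically restored by the visit. Under the written definition:

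observed success = p + f(1 − p)

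With the same f in both arms, the observed difference is (1 − f) × the true difference.

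**Assumed inputs.** True success is 90% (LSC) and 75% (LILS), which puts LILS exactly at the margin. The documents give no value for f; 0 to 0.4 is shown.

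**Calculation.** Exact binomial probability, over all outcomes with 86 per arm, that the lower Wald 95% limit for LILS minus LSC exceeds -15 points:

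| f, both arms | Observed LSC | Observed LILS | Difference (points) | P(noninferiority concluded) |
|---|---|---|---|---|
| 0 | 90% | 75% | -15.0 | 3.0% |
| 0.1 | 91% | 77.5% | -13.5 | 5.4% |
| 0.2 | 92% | 80% | -12.0 | 9.5% |
| 0.3 | 93% | 82.5% | -10.5 | 16.3% |
| 0.4 | 94% | 85% | -9.0 | 27.1% |

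For example, at f = 0.2 observed LILS success is 0.75 + 0.2 × 0.25 = 0.80. With 89 per arm the probabilities at f = 0, 0.1 and 0.2 are 2.8%, about 5% and 9.3%, so the choice of 86 or 89 matters little.

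**When the direction changes.** In general the shift in the observed difference is f(LILS) × failure(LILS) − f(LSC) × failure(LSC).

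- Equal failure and equal f: the shift is zero. With 10% failure in both arms the difference stays 0.
- Only LSC failures retreated, f = 0.2: LSC is observed at 92% and LILS at 75%. The difference becomes -17 points, and the chance of concluding noninferiority falls from 3.0% to 1.3%.
- With failure of 25% v 10%, the shift turns against LILS only when f(LSC) exceeds 0.25/0.10 = 2.5 times f(LILS). With equal failure rates, any excess of f(LSC) is enough.

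**The case against.** The strongest objection is that the article is silent on retreatment rather than wrong about it, and that an analysis plan not shown may class retreatment as failure. The mention of recurrence in the dropout assumption suggests that recurrence was thought of as an event. This stands in part: no sentence says that a re-operated woman is a success, and a reader who takes the document to say so goes too far. She scores as one only if the second operation restored her anatomy. But the article gives the primary endpoint in full, twice, and that definition taken literally yields this result. A plan that scored her as a failure would have to change the definition, not fill in a detail.

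A reader might also infer that the comparison is biased toward noninferiority. The documents do not support that without conditions. They give neither failure rates by arm nor retreatment rates, and the calculation shows no bias in one setting and bias against LILS in another.

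The larger figures deserve caution too. The endpoint counts as failure any site lower than 1 cm above the hymen, including descent that stays inside it. Nothing in the document suggests that 20% to 40% of such failures would be retreated and restored within a year; at f = 0.05 the error is 4.0%. Further, a failure still present at an earlier visit is scored as a failure at that visit. Only women who fail and are restored between two consecutive visits escape every assessment.

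**Conclusion.** The point holds in a conditional form. The written definition scores a woman whose failed repair was successfully redone before the visit as a success of her randomized operation. Whether this favours noninferiority depends on two things the documents do not give: that LILS truly fails more often, and that its failures are retreated about as often as LSC failures. Under those conditions, at the margin with 86 per arm, the false noninferiority rate goes from about 3% to 5% at one tenth retreated and restored, and to 9.5% at one fifth. The size in this trial is unknown. The definition should nevertheless be corrected, because a truly worse LILS is the case the noninferiority test has to guard against.

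**What to change.** In both places where success is defined, add that a woman who has had repeat surgery for recurrent prolapse since the index operation counts as a failure at that and all later visits. State in advance how non-surgical retreatment is classed; making every conservative treatment a permanent failure by default would be too broad for an anatomical endpoint. Report the POP-Q-only result as supportive. This is a rule for classifying outcomes and changes nothing in patient care.

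The cost is small but not nil. Repeat prolapse surgery must be recorded explicitly at each visit: Data collection names questionnaires, a clinical examination with POP-Q, and long-term complications, so it should not be assumed that retreatment is already captured. Observed success may be slightly lower in both arms. Trial status gives a start in March 2016 with primary follow-up due by March 2018, so the change should be documented and dated as an amendment to the endpoint of a running trial.

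### The noninferiority endpoint, anatomical success, is defined by two criteria that disagree for every stage 1 woman and for a woman at exactly −1 cm

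*Protocol article*

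**What the plan says.** In the protocol article, under Primary and secondary outcomes, anatomical success is "defined as less than stage 1 (all vaginal sites at least 1 cm above the hymen on Valsalva", scored with POP-Q. Under Sample size and power considerations the definition returns in the same double form: "Surgical anatomical success rate is defined as less than stage 1 (all vaginal sites at least 1 cm above the hymen on Valsalva".

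The outcomes section also gives the measurement scale: "points above the hymen are negative and those below are positive; vaginal support at the level of hymen is represented as ‘0 cm". Entry uses the same staging system (Study population and recruitment): "All women seeking treatment for symptomatic POP with uterine descent POP-Q stage 2 or higher will be considered for inclusion".

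The sample-size section gives the endpoint its role: "Anatomical success rate at each follow-up point assessed by a POP-Q-examination in both study groups will be considered as primary outcome". Noninferiority is concluded if the lower 95% confidence limit for the difference in success rates lies above −15%. The planning success rate is 90% within one year, set against a review that reported 78% to 100% for LSC.

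**The concern.** The definition has two halves, a stage and a distance, and the second is offered as the meaning of the first. They do not describe the same women. The stage wording admits only the lowest category of the scale. The bracket admits anyone with no point lower than −1 cm.

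This endpoint decides the trial. With two criteria on the page, two success rates can be computed from the same examinations, and either can be defended from the published text. If the choice is made after outcomes are known, the test is no longer fully prespecified. The planning rate and the margin are affected too: 15 points of difference in having no descent at all is not the same clinical statement as 15 points of difference in descent no lower than −1 cm.

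**Working it through.** **Inputs.** The two halves of the definition and the centimetre scale come from the outcomes section. The entry stage comes from the recruitment section. The 90%, the 78% to 100% range, 89 per group, 20% loss, 107 per group and the 15-point margin come from the sample-size section. The POP-Q cut-offs are not printed in the article; they belong to the scoring system it names: stage 0 is no descent, stage 1 is a lowest point more than 1 cm above the hymen, and stage 2 is within 1 cm either side of it.

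**Step 1: classify women under each half.**

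| Lowest vaginal point | POP-Q stage | By the stage wording | By the bracket |
|---|---|---|---|
| No descent | 0 | success | success |
| −2 cm | 1 | failure | success |
| Exactly −1 cm | 2 | failure | success |
| 0 cm, or below the hymen | 2 or higher | failure | failure |

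The disagreement runs one way. Every success by the stage wording is also a success by the bracket, and the bracket adds all of stage 1 and the stage 2 women at exactly −1 cm. The success rate by the bracket is therefore at least as high. The gap is the share of women in the two middle rows, which the article does not give.

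**Step 2: does the conflict depend on the cut-offs?** The main conflict does not. On any staging scale that starts at 0, being below stage 1 leaves only the lowest category, while the bracket tolerates descent to −1 cm. The point about exactly −1 cm does need the cut-off between stages 1 and 2.

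**Step 3: the plan's own sample size.** For equal rates p in both arms, n per group = 2p(1−p)(1.96 + 0.842)² / 0.15².

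- p = 0.90: 0.18 × 7.849 / 0.0225 = 62.8, so 63.
- p = 0.85: 0.255 × 7.849 / 0.0225 = 88.95, so 89.

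The stated 89 is not reproduced from the stated 90%. That is a separate matter and does not bear on this point.

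**Step 4: how power moves with the success rate (illustration only).** Evaluable women per group: 107 × 0.8 = 85.6, taken as 86. Power = Φ(0.15 / √(2p(1−p)/86) − 1.96).

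- p = 0.90: SE = 0.0457; 0.15/SE = 3.28; Φ(1.32) = 91%.
- p = 0.85: SE = 0.0545; 0.15/SE = 2.75; Φ(0.79) = 79%.
- p = 0.78: SE = 0.0632; 0.15/SE = 2.37; Φ(0.41) = 66%.

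These rates stay within the range the article cites. They show that power is sensitive to the rate, not what either definition would yield.

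**The case against.** The strongest reply is that the intent is clear. The centimetre gloss appears in both places, a planning rate of 90% looks more natural for a rule that tolerates some descent, and at 90% the power is about 91%. On this view the stage wording is a slip. That is plausible, but the text does not settle it. Even if stage 0 or 1 was meant, the halves still differ at exactly −1 cm: the bracket counts her a success, while the cut-offs put her in stage 2. An analysis plan not shown here may choose one half, but it would then contradict the other half of the published definition. This is a stated rule that conflicts with itself, not a detail left out.

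Three stronger inferences are tempting, and the article does not support them.

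- **That a woman re-operated for recurrence before a visit is scored a success.** The article is silent on retreatment, which may properly be handled in the full protocol or analysis plan. Recurrence is listed separately in the study objective, and the sample-size section speaks of loss to follow-up without recurrence, so it may be tracked as an event.
- **That the 90% can fit only one definition.** The success definitions behind the cited review are not visible. The rate may match either half, neither, or a mixture.
- **That the trial is underpowered under the strict reading.** No stage 0 success rate is given, so any figure would be assumed.

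**Conclusion.** Wrong as written. The endpoint that carries the noninferiority decision is defined in two incompatible ways, in both sections where it is defined, and no other section says which prevails. Every stage 1 woman, and any woman at exactly −1 cm, is classified in opposite ways by the two halves.

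The contradiction itself rests on the article's wording. The status of exactly −1 cm rests on the POP-Q cut-offs, which the article adopts by name. The size of the effect on the success rate, and so on the trial's conclusion, cannot be derived from the article; the power figures show sensitivity only. The established harm is the ambiguity: an endpoint rule that could be chosen with data in view, and a planning rate not tied to a definition.

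**What to change.** Before any unblinded analysis, state one criterion as a centimetre threshold together with the POP-Q stage that matches it, and say how exactly −1 cm is classed.

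- If stage 0 or 1 is meant, the bracket must require every vaginal point to be more than 1 cm above the hymen, which excludes −1 cm.
- If the bracket is kept as it stands, which includes −1 cm, the stage wording must be dropped or corrected.
- If stage 0 alone is meant, the bracket must go.

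The first option should not be presented as what the present bracket already says, because it changes the class of a woman at −1 cm. Use the chosen wording identically in the outcomes and sample-size sections, and confirm that the 90% planning rate refers to that definition. If it does not, restate the rate and recheck the sample size.

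The cost is a wording amendment in two places and a check of the source of the 90%. A POP-Q examination is already planned at every follow-up visit, so no new data are needed.
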